## Abstract

**Background:**

Family caregivers (FC) often experience higher distress levels than their relative with cancer. Many cancer centers have implemented distress screening programs, but most of them concentrate their efforts on patients, with little attention to their FC. To fill this gap, a pragmatic intervention has been designed to improve supportive care for FC of patients with lung cancer. This article describes the study protocol of a single-center randomized controlled trial to assess its effectiveness.

**Methods/design:**

A total of 120 lung cancer patients and their FC are randomly assigned to the experimental group (exposed to intervention, *N* = 60) or to the control group (usual care, *N* = 60). The intervention includes: (1) systematic FC distress screening and problem assessment near their relative’s cancer diagnosis, and every 2 months, (2) privileged contact with an oncology nurse (ON) away from the patient to address FC problems and (3) liaison by the ON with the family physician of FC reporting high distress (thermometer score ≥5/10), or problems relying on FP expertise. In both groups, FC, patient and process-of-care outcomes are measured at baseline and every 3 months, up to 9 months. The primary endpoint is FC distress measured by the Hospital Anxiety and Depression Scale (HADS) and the Psychological Distress Index used in the Quebec Health Survey (PDQHS). Individual interviews with 10 FC and a focus group with the oncology team will be conducted at the study end to further document the effectiveness of the intervention and its impact on quality of life (for FC) and practice organization (for the oncology team).

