## Objectives

The main objective of this study is to implement and assess the effectiveness of an intervention integrating community-based primary care with oncology care to improve supportive care for FC of lung cancer patients. More specifically, this trial aims to assess the effectiveness of the intervention on: (1) *FC outcomes*: distress (primary outcome), anxiety, depression, quality of life (QoL), needs, burden, perception of health, preparedness in caregiving, social support, care satisfaction, (2) *Patient outcomes*: distress, anxiety, depression, QoL, pain/other symptom relief, (3) *Care process outcomes*: FC and patient utilization of services. In addition, a qualitative component of the study will further document, in the experimental group, FC-perceived usefulness of the intervention and its effects on distress/QoL, and in the oncology team, the perceived usefulness of the intervention and its effects on their practice and organization of care.

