**Fig. 3 Fig3:**
[figure not shown]
Trial flow diagram

As FC distress is the primary outcome in this study, the sample size was calculated from the mean scores of distress found in a prior study conducted by our team with a similar population of FC of patients with lung cancer (unpublished abstract presented at the 16th World Congress of Psycho-Oncology, Lisbon, Portugal, 23 October 2014). Based on FC distress scores of respectively 13.7 ± 7.0 at the Hospital Anxiety Depression Scale (HADS) (range = 0–42) and of 23 ± 16 at the Psychological Distress Scale used in the Quebec Health Survey (PDSQHS) (range = 0–100), a sample size of 120 FC (60 per group) was calculated. Considering a 5% *α* error, a power of 80% and an anticipated withdrawal rate of 20% (due to patient deterioration or death), this sample size allows to detect a 33% difference in distress scores between the two groups which is considered clinically significant.

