### Procedures and data collection

At a regular visit of the patient who is most often accompanied by their FC, the OPN briefly explains the study to them and asks permission to transfer their phone number to the study team. Then, a research professional contacts them to present the study more extensively, get their agreement to participate and set an appointment with them to sign the Consent Form and begin the data collection with them. In both groups, the research professional interviews separately patients and FC at baseline and at 3-month intervals, for a maximum of 9 months, or until the patient’s death (maximum of four data collections), thus minimizing missing data (Fig. 3). Validated tools are used to collect all the study outcomes. At baseline, FC respond to basic questions related to their personal and medical characteristics. They also complete the following validated questionnaires:Primary outcomes:
*Distress* measured by two instruments: (1.1) the HADS [33, 34], a 14-item instrument specifically designed to evaluate distress, anxiety and depression. For each item, the scale varies from 0 (most of the time) to 3 (never). Using the standard criteria suggested by authors of this instrument, distress scores are converted into two categories (absence/presence of distress) while anxiety and depression scores are converted into three (absence/suspected/significant anxiety or depression); (1.2) the global score of the abbreviated version of the PDSQHS [35, 36]. This14-item instrument was derived from the Psychiatric Symptoms Index [37] and has been used in the Quebec general population to estimate the prevalence of clinically significant distress (scores ≥80th percentile), so it permits the comparison of proportions of FC with high distress levels to the ones found in the general population. The PDSQHS scale varies from 1 (never) to 4 (very often).
Secondary outcomes:
*Needs*. The Home Caregiver Need Survey [38] is a 25-item tool covering four categories of needs (informational, practical, emotional and spiritual). FC indicate, for each need, its perceived importance, on a 0 (not important) to 4 (extremely important) scale, and how well it is satisfied (0 = unsatisfied to 4 = completely satisfied).
*Psychological burden*. The French version of the Caregiver Burden Scale in End of Life Care (CBS-EOLC) [39] is a 16-item instrument validated among FC who assist cancer patients in palliative phase. Items vary from 1 (never) to 4 (very often).

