### Analysis

The quantitative analysis plan first includes an evaluation of the adherence to the planned intervention by verifying for each FC from the experimental group: (1) the proportion of planned screening tools actually completed, (2) the proportion of liaisons with FP, (3) a descriptive analysis of all interventions performed by the ON (number of encounters, referrals, provision of educational material, etc.). Then, FC primary and secondary outcomes will be compared between the experimental and control groups at each data collection period. In addition, mixed models for repeated measures will be constructed with FC, patient and process-of-care outcomes to assess the intervention effectiveness. These analyses of variance for repeated measures will compare the fluctuation over time of FC distress and other variables between the experimental and control groups. Whenever significant changes are found within one group for certain outcomes over time, the mixed models for repeated measures will help to identify when the change occurred. Finally, McNemar tests will be used to compare FC and patient distress.

The qualitative analysis will consist in content analysis of the recordings of FC individual interviews and the focus group with the OT, based on Miles and Huberman methodology [45], to further document the perceived usefulness of the intervention and its effect on FC QoL and on the OT practice and organization of care. Each interview will be independently analyzed by a research professional and one researcher to ensure interobserver reliability. In case of disagreement, perceptions will be reviewed until a consensus is reached.

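### Two unranked primary distress instruments, compared at every visit and again in mixed models, with one 5% alpha and no stated rule for which result decides the trial

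*Protocol article*

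**What the plan says.** The protocol article is the only document available. I write PDSQHS for its second distress instrument throughout.

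- **One outcome or two.** The Objectives list caregiver outcomes as "distress (primary outcome), anxiety, depression, quality of life (QoL), needs, burden", so distress is a single primary outcome. The abstract measures it with two scales: "The primary endpoint is FC distress measured by the Hospital Anxiety and Depression Scale (HADS) and the Psychological Distress Index". Procedures and data collection puts both under a plural heading of primary outcomes: "Distress* measured by two instruments: (1.1) the HADS [33, 34], a 14-item instrument", with PDSQHS following as item 1.2. Neither is ranked above the other.
- **Visits.** Assessments are made "at baseline and at 3-month intervals, for a maximum of 9 months, or until the patient’s death (maximum of four data collections", so there are three after baseline.
- **Analyses.** The Analysis section says "FC primary and secondary outcomes will be compared between the experimental and control groups at each data collection period". It continues: "In addition, mixed models for repeated measures will be constructed with FC, patient and process-of-care outcomes to assess the intervention effectiveness". These models "will compare the fluctuation over time of FC distress and other variables between the experimental and control groups"; no visit or contrast is singled out.
- **Alpha.** It appears once, in the sample-size paragraph under Study population: "Considering a 5% *α* error". That paragraph gives planning means and SDs for both instruments and does not divide the 5% between them.

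**The concern.** A primary analysis has to say which result answers the question. Here there are two instruments, three post-baseline visits and two kinds of analysis, and nothing orders them. Two consequences follow.

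- The 5% and 80% used to size the trial describe one test of one variable. They carry over to the actual decision only under a success rule that the protocol does not give.
- If HADS and PDSQHS disagree, or month 3 and month 9 disagree, the primary question has no defined answer.

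Timing matters because the Study population section says that there is no blinding and that the research team knows the allocation. A deciding test chosen late could be chosen with knowledge of how the arms compare.

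**Working it through.** **Inputs from the protocol.** HADS 13.7, SD 7.0; PDSQHS 23, SD 16; difference 33%; alpha 5%; power 80%; withdrawal 20%; 60 per group, so 60 × 0.8 = 48 evaluable. Two instruments, three post-baseline visits.

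**Assumptions, because the protocol gives no figure.** Tests are two-sided. The correlation is 0.3-0.8 between visits (exchangeable or first-order autoregressive) and 0.5-0.9 between instruments.

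**1. The plan's own sample size.** n per group = 2(1.960 + 0.842)²/d² = 15.70/d².
- HADS: difference 0.33 × 13.7 = 4.52; d = 4.52/7.0 = 0.646; n = 37.6, so 38; 38/0.8 = 47.5, so 48 per group, 96 in total.
- PDSQHS: difference 0.33 × 23 = 7.59; d = 7.59/16 = 0.474; n = 69.8, so 70; 70/0.8 = 87.5, so 88 per group, 176 in total.

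The stated 120 matches neither, so it does not show which instrument the trial was sized on.

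**2. Power at 48 evaluable per group.** Power ≈ Φ(d√(48/2) − 1.960).
- HADS: 0.646 × 4.899 − 1.960 = 1.20, giving 89% (88% with the t distribution).
- PDSQHS: 0.474 × 4.899 − 1.960 = 0.36, giving 64% (63% with the t distribution).

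**3. Either instrument suffices, at one contrast.** With independent tests the error would be 1 − 0.95² = 9.75%. Simulating correlated null z-statistics (300,000 draws per setting) gives 7.0-9.2%.

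**4. Both must succeed, at one contrast.** Error is 0.9-3.0%. Joint power cannot exceed the weaker component, so it is at most 63-64%. If both must be significant at the same visit but any visit will do, error is 2.1-8.3%.

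**5. Any significant result counts.** With independent tests, 2 × 3 = 6 visit tests give 1 − 0.95⁶ = 26.5%. By simulation:

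| Tests counted | Chance of at least one false positive |
|---|---|
| Six post-baseline visit tests | 13.6-24.0% |
| The six plus one group-by-time test (3 df) per instrument | 19-27% |
| Six visit tests, only results favouring the intervention | 6.8-12.3%, against a nominal 2.5% |

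**6. Splitting alpha, 0.025 per instrument, at one contrast.** Error is 3.6-4.7%. Power at 48 per group is about 82% for HADS and 53% for PDSQHS. A split would need 58 and 107 per group respectively after allowing for withdrawal. The 58 is close to 60, but the text states 5% and the PDSQHS figure is far off, so this is not evidence that a split was planned.

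**The case against.** A reader might infer that the protocol prescribes unadjusted 5% tests at every visit, any of which wins the trial, and so an error rate three to four times nominal. The document does not support that.

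- **Unadjusted is an inference from silence.** The 5% is stated only for the sample size. The Analysis section gives no level per test and neither describes nor excludes an adjustment. This is a condensed article, and an analysis plan that is not shown may contain one.
- **No any-result-wins rule is stated.** The abstract joins the instruments with an and, and the sample-size paragraph gives figures for both, so requiring both is an equally open reading. It keeps error below nominal at one contrast.
- **The mixed models may be meant to decide.** Only they are given the purpose of assessing effectiveness. The visit comparisons also cover baseline and secondary outcomes, which fits a supportive role. If the models decide, the six-test figures do not describe the primary decision.
- **A fixed multiple is not available.** It depends on assumed correlations. The six visit tests alone span 2.7-4.8 times nominal, and adding the group-by-time tests makes it 3.8-5.4 times.

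All four points stand, and they make the error rate conditional. They do not remove the gap. Covariance structure and adjustment details can wait for an analysis plan, but the primary variable and its deciding contrast define what the trial tests and what its sample size refers to. The article also does more than stay silent: it sets out two primary instruments and two layers of comparison on one undivided alpha. Neither simple reading at an undivided 5% preserves both design figures, since the either-instrument rule exceeds 5% and the both-instruments rule falls short of 80% power.

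**Conclusion.** The concern holds as a missing decision rule, not as a demonstrated fixed inflation. The protocol leaves open the deciding instrument, visit and contrast, and whether one or both instruments must succeed; no adjustment is stated. The consequence is about 7-9% error under an either-instrument rule at one contrast, and roughly 14-27% if any significant visit or model result counts. Under a both-instruments rule at one contrast, error is at or below nominal with power no better than about 63-64%. The error rates rest on the assumed correlations and two-sided testing. The power figures follow from the protocol's own means, SDs, 33% difference and 20% withdrawal.

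**What to change.** By amendment or in the analysis plan, before any between-arm outcome data are examined (the trial is open-label, so a deadline tied to unblinding would protect nothing):

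1. Name one primary test: the between-arm difference in continuous HADS total, from the repeated-measures mixed model, at one pre-named contrast (for example one named visit, or the average of the post-baseline visits).
2. Test PDSQHS at 5%, at the same contrast, only if HADS is significant.
3. Label the per-visit comparisons and all other outcomes as supportive, and report them with confidence intervals.

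HADS goes first because it is the instrument for which the trial has at least its stated power (about 88-89% at 48 per group, against 63-64% for PDSQHS). A co-primary rule or a split alpha would also define the decision, but at the power shown in steps 4 and 6 of the working.

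The cost is a few sentences, with no extra participants or data. The downside is that PDSQHS cannot rescue a negative HADS result. The trial status was still recruiting at publication, so on the document's own account the rule could still be fixed in advance.

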**Discussion:**

This trial will assess the effectiveness of an innovative intervention based on interprofessional collaboration between primary care and oncology care. It targets a population in great need, yet often neglected, and has the potential to clearly improve patient and caregiver experience of cancer care, and reduce the burden of disease.

**Trial registration:**

ClinicalTrials.gov, ID: NCT02531464. Registered on 15 July 2015.

**Electronic supplementary material:**

The online version of this article (doi:10.1186/s13063-017-2044-y) contains supplementary material, which is available to authorized users.

## Background

A diagnosis of cancer is emotionally threatening not only for patients but also for their family caregivers (FC) who witness and share much of the illness experience of their relative [1]. Along the cancer care trajectory, FC play a critical role in providing ongoing homecare and assistance to their loved one [1]. However, they are often unprepared to play their role and may experience growing levels of distress, as their relative’s condition deteriorates. Even though many FC are coping quite well, studies show that 10 to 50% of them report high distress [2, 3] which is often more severe than in patients [2, 4–7], and it may persist over time, with a potential impact on their physical, emotional and social health [1, 4, 8]. FC of lung cancer patients are particularly vulnerable [7] and likely to be distressed [9–13] because of a rapid evolution [2, 8, 14] and decline in their relative’s functional status associated with symptoms and treatment side effects [1, 15–17].

FC may often feel unsupported in their role [18] and would need more information and tips to fulfill it [18]. Their unmet needs may compromise their quality of life (QoL) [19] and contribute to their distress [20], but also they may adversely impact on their relative’s distress [21]. Because of the interrelation of the patient-FC dyad experience, identifying and meeting FC needs should be considered as an integral part of cancer services [22–25]. It is recommended to assess FC distress and needs early after diagnosis, and to reassess them regularly with cancer progression [26, 27] in order to support them and help them play their role in patient assistance and ongoing care throughout the care trajectory. However, little is known on the most effective interventions to develop and how to implement them into routine practice [13, 27].

As recommended by many expert groups and health authorities around the world [22–25], many cancer centers have implemented distress screening programs. However, most of them concentrate their efforts mainly on patients. In order to fill this gap, an intervention was developed to improve supportive care for FC.

### Development of the intervention

The multifaceted intervention was developed according to the knowledge gained from the academic literature, from previous research [28] and from recommendations of expert groups and health authorities [22–25]. The Screening for Distress tool currently used for cancer patients in Quebec, Canada (including the Distress Thermometer with the Canadian Problem Checklist and the Edmonton Symptom Assessment Scale [29, 30]) was adapted to the FC context (Fig. 1). Then, a pilot study was conducted, consisting in individual interviews with 12 FC of patients at different phases of their lung cancer (near diagnosis, during chemo/radiation therapy, after the end of treatments), to get their comments and impressions regarding this tool and the other components of the intervention. FC also gave their opinion on the most appropriate timing and frequency for completing the Screening for Distress tool, and were invited to suggest any other strategies that they would consider useful to fulfill their needs. In addition, a focus group was conducted with members of the IUCPQ oncology team and their decision-makers, (where the intervention is tested), to ensure its acceptability and feasibility in their practice. IUCPQ is a tertiary care center in cardiology and pulmonology in Quebec City (Quebec, Canada) where more than 700 new patients with lung cancer are followed each year. The oncology team (OT) is composed of pulmonologists responsible for the treatment of these patients, oncology pivot nurses (OPN) who play a role of resource person and cancer navigator for patients and their family (each patient has a designated OPN to refer to whenever needed), oncology nurses, social workers, a psycho-oncologist, pharmacists and nutritionists. Finally, a focus group with eight family physicians (FP) from different community-based practice settings (private clinics, family medicine teaching units, community health centers) was conducted to ensure that the intervention was also acceptable and feasible in their practice.

**Fig. 1 Fig1:**
[figure not shown]
Distress Screening tool adapted to the family caregiver (FC) context

With the agreement of participants, individual interviews and focus group discussions were recorded to facilitate data collection. A content analysis of the recordings was performed independently by a research professional and one researcher to identify the modifications to the intervention that were suggested by the different participants. They compared their notes and jointly produced a summary discussed with the research team that served to adapt and refine the multifaceted intervention accordingly.

## Objectives

The main objective of this study is to implement and assess the effectiveness of an intervention integrating community-based primary care with oncology care to improve supportive care for FC of lung cancer patients. More specifically, this trial aims to assess the effectiveness of the intervention on: (1) *FC outcomes*: distress (primary outcome), anxiety, depression, quality of life (QoL), needs, burden, perception of health, preparedness in caregiving, social support, care satisfaction, (2) *Patient outcomes*: distress, anxiety, depression, QoL, pain/other symptom relief, (3) *Care process outcomes*: FC and patient utilization of services. In addition, a qualitative component of the study will further document, in the experimental group, FC-perceived usefulness of the intervention and its effects on distress/QoL, and in the oncology team, the perceived usefulness of the intervention and its effects on their practice and organization of care.

## Methods/design

A two arm-randomized controlled trial is conducted at a single center, the IUCPQ Pulmonary Oncology Clinic, to assess the effectiveness of the intervention (Fig. 2).

**Fig. 2 Fig2:**
[figure not shown]
The multi-faceted intervention

### Description of the intervention

In the current practice at the IUCPQ Oncology Clinic, there is a systematic distress screening program for patients, but not for FC. In their role towards patients and their family throughout the cancer care trajectory, may provide some support and information to FC and, in rare occasions, refer them to appropriate resources. However, most of their interventions target patients, and only few FC receive support services. There is no systematic distress screening and problem assessment for FC, nor any standardized service and resource specifically dedicated to them. The study intervention directly targets FC of patients with lung cancer and aims to increase the support provided to them. In order to prevent contamination of the control group, an oncology nurse (ON) with the training of an OPN [31, 32] has been recruited specifically to administer the intervention to FC randomly assigned to the experimental group. The ON intervenes in addition to the usual care provided by an OPN to patients and their family. The finalized intervention includes three components and is summarized in Fig. 2:
*Systematic distress screening and needs/problems assessment of family caregivers by the oncology nurse*
FC from the experimental group complete the adapted Screening for Distress tool early after the diagnosis of their relative, and every 2 months during the 9-month study. Whenever possible, they complete this tool when they accompany their relative at a regular visit to the clinic. Otherwise, arrangements are made by the ON to either schedule a specific visit for FC distress screening or mail them a copy of the screening tool and complete it with them by phone. The ON reviews the results of the Screening for Distress tool
*Privileged contact of the family caregiver with the oncology nurse*
The ON meets all FC away from their relative, after their first completion of the distress screening and needs/problems assessment tool. This professional discusses with them results of this tool, and further assesses their needs in order to plan with them individualized problem-solving strategies, and, if necessary, refers them to professional resources from the IUCPQ Oncology Clinic or the community. The training as an OPN provides the ON the basic skills to support FC, acknowledging that it is normal for them to go through different emotions (anxiety, fear, sadness, helplessness, etc) in their situation, and counsels them on the importance of taking care of them and preserving time for them, while accompanying their relative. The ON provides community resources and educational material (in addition to what is usually given) related to their caregiving role, and helps them to become better prepared and more proactive in their role, also answering all remaining questions asked by FC. Then, every 2 months, the ON reviews FC results of the screening tool and meets those who present a high level of distress (thermometer score ≥5/10) or who indicate needing help. The ON follows-up on prior strategies put in place to help FC and adjusts them to the current situation. So the ON acts as a resource person for FC throughout the follow-up in oncology
*Liaison by the oncology nurse with the FC family physician*
For FC reporting high levels of distress (thermometer score ≥5/10) or experiencing problems relevant to FP expertise, the ON transfers to their FP, information on their identified needs and level of distress, and also provides to them information on any strategy put in place or reference to other health professionals to respond to FC needs. The ON invites FP to give an appointment to their patient, and facilitates a shared follow-up of the FC when needed. If FC continue to present high levels of distress or many needs/problems at subsequent screenings, the ON transfers the information to their FP and organizes another appointment/follow-up. Most communications between the ON and FP occur by fax, but they may also communicate by phone if needed.

